## Study Design

This is a prospective, open-label, single arm, multi-centre interventional study to assess the clinical efficacy and safety of olaparib maintenance monotherapy as the tablet formulation in PSR high grade (serous or endometrioid) epithelial ovarian cancer patients (including patients with primary peritoneal and / or fallopian tube cancer).

Figure 1 Study Flow Chart

Notes: OC ovarian cancer; PR partial response; CR complete response; PFS progression free survival; PFS2 time to second progression; TFST time to first subsequent treatment; TSST time to second subsequent treatment; OS overall survival; TDT time to discontinuation of treatment;

Patients will be assigned to olaparib tablets p.o. 300 mg twice daily. They should initiate olaparib treatment within 8 weeks after their last dose of chemotherapy (last dose is the day of the last infusion).

Patients must have clinical and objective radiological tumour assessments according to RECIST 1.1 criteria at baseline and every 12 weeks relative to date of enrolment, until objective radiological disease progression as determined by the investigator. Patients could continue to receive olaparib for as long as determined by the investigator, until objective radiological disease progression or as long as in the investigator’s opinion they are benefiting from treatment in relation to other clinical assessments and they do not meet any other discontinuation criteria.

Once a patient has discontinued olaparib she will be managed as per local clinical practice but will remain in the study and data will be collected on subsequent treatments, progression and survival.

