^d^ Safety blood samples do not need to be repeated on Day 1 of study treatment if assessed at least 3 weeks after the last dose of chemotherapy but within 7 days before starting study treatment, unless the investigator believes that it is likely to have changed significantly. Coagulation test should be performed at screening and if clinically indicated. For a list of all required laboratory tests please refer to Section [5.2.1](#_Laboratory_safety_assessments).

^e^ Pregnancy tests on blood or urine samples will be performed for women of childbearing potential within 28 days prior to the start of study treatment, on Day 1 of the study prior to commencing treatment, at the time points shown in Table 2 during study treatment and at the 30 day follow up visit If results are positive the patient is ineligible/must be discontinued from study treatment immediately.

^f^ Follow-up very 12 weeks after start of treatment until objective disease progression as defined by RECIST 1.1, up to 72 weeks, then every 24 weeks relative to date of enrolment. Any other sites at which new disease is suspected should also be appropriately imaged. If an unscheduled assessment was performed and the patient has not progressed, every attempt should be made to perform the subsequent assessments at their scheduled visits.

^g^ All ongoing adverse events/serious adverse events (AEs/SAEs) and any new AEs/SAEs identified during the 30 calendar days follow up period after last dose of study medication must be followed to resolution.

^h^ Sufficient study treatment should be dispensed for at least each treatment period plus overage.

^i^ All anti-cancer treatments (including, but not limited to, chemotherapy and targeted agents), and the investigators opinion of response to them plus the date of progression, post discontinuation of study treatment need to be recorded.

^j^ Only patients on treatment post progression are required to undergo this procedure.

^K^ Patients on treatment post progression are only required to undergo these procedures.

| Table 3 Study Schedule –Follow up Post Discontinuation of Study Treatment | | |
| --- | --- | --- |

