| Visit Number | **Off treatment follow up**  **Study treatment discontinued due to reasons other than disease progression**  **Visits every 12 weeks Follow up for 1st progression Tumour assessment visits every 12**  weeks or 24 weeksa | **Time to second progression (PFS2) and Survival for:**  • Patients who have discontinued study treatment due to disease progression  • Patients who have progressed off treatment  • Patients who were on study treatment post progression and / or after primary (PFS) analysis who subsequently discontinued study treatment  Every 12 weeks post discontinuation of study treatment |
| Visit Window | ±7d | ±7d |
| Blood sample for disease specific marker (CA-125) | X |  |
| Tumour Assessment (CT or MRI according to modified RECIST v1.1) a | X |  |
| Adverse Events | X | X |
| ECOG performance status | X | X |
| Subsequent cancer therapy following discontinuation of study treatment ^b^ | X | X |
| Time to second progression |  | X |
| Survival ^cd^ | X | X |

a RECIST follow-up assessments will be performed every 12 weeks (±1 week), up to 72 weeks, then every 24 weeks (±1 week) relative to date of enrolment. Follow-up assessment will include CT or MRI assessments of abdomen and pelvis for all patients. Follow-up chest CT will be performed (in those patients with thoracic lesions or upper abdomen lymphadenopathy identified at baseline assessment). Any other sites at which new disease is suspected should also be appropriately imaged. Patients must be followed until RECIST disease progression. If an unscheduled assessment was performed and the patient has not progressed, every attempt should be made to perform the subsequent assessments at their scheduled visits. Following disease progression further RECIST assessments will not be performed and assessment of disease will be as per local clinical practice.

b All anti-cancer treatments (including, but not limited to, chemotherapy and targeted agents), and the Investigators opinion of response to them and the date of progression need to be recorded.

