## Efficacy assessments

### CT and MRI scans tumour assessments (Modified RECIST 1.1)

Following the baseline assessment, subsequent tumour assessments according to modified RECIST 1.1 should be performed every 12 weeks (±1week) for the first 72 weeks and then every 24 weeks (± 1 week) thereafter, relative to the date of enrolment, up to objective disease progression by RECIST.

For those patients with no evidence of disease at baseline, following a clinical complete response to chemotherapy, progression is defined by the detection of new lesions on follow up radiological assessments (modified RECIST 1.1).

The imaging modalities used for RECIST assessment will be CT or MRI scans of the neck, chest, abdomen and pelvis with other regions as clinically indicated for the assessment of disease. Any other sites at which new disease is suspected should also be appropriately imaged. The methods of assessment of tumour burden used at baseline must be used at each subsequent follow-up assessment.

Radiological examinations performed in the conduct of this study should be retained at site as source data.

All treatment decisions will be based on site assessment of scans.

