### Tumour Evaluation

RECIST 1.1 criteria will be used to assess patient response to treatment by determining progression free survival (PFS) times according to the RECIST 1.1 guideline (Eisenhauer et al 2009).

The methods of assessment of tumour burden used at baseline CT or MRI scans of neck, chest, abdomen and pelvis must be used at each subsequent follow-up assessment. Any other areas of disease involvement should be additionally imaged based on the signs and symptoms of individual patients.

Following the baseline assessment, efficacy for all patients will be assessed by objective tumour assessments every 12 weeks after enrolment, up to 72 weeks, then every 24 weeks until objective disease progression as defined by RECIST 1.1. Any other sites at which new disease is suspected should also be appropriately imaged.

If a patient discontinues treatment (and/or receives a subsequent cancer therapy) prior to progression then the patient should still continue to be followed until objective disease progression as defined by RECIST 1.1.

Categorisation of objective tumour response assessment will be based on the RECIST 1.1 criteria of response: CR (complete response), PR (partial response), SD (stable disease) and PD (progression of disease). Target lesion (TL) progression will be calculated in comparison to when the tumour burden was at a minimum (i.e. smallest sum of diameters previously recorded on study). In the absence of progression, tumour response (CR, PR, SD) will be calculated in comparison to the baseline tumour measurements obtained before starting treatment.

For patients with non-measurable disease only at baseline, categorisation of objective tumour response assessment will be based on the RECIST 1.1 criteria of response: CR (complete response), PD (progression of disease) and Non CR/Non PD.

If the Investigator is in doubt as to whether progression has occurred, particularly with response to NTL (non-target lesion) or the appearance of a new lesion, it is advisable to continue treatment until the next scheduled assessment or sooner if clinically indicated and reassess the patient’s status. If repeat scans confirm progression, then the date of the initial scan should be declared as the date of progression.

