### Primary endpoint

PFS is defined as the time from first dose of olaparib until the date of investigator assessed disease progression according to RECIST 1.1 criteria or death (by any cause in the absence of disease progression) regardless of whether the patient withdraws from therapy or receives another anticancer therapy prior to disease progression. Patients who have not progressed or died at the time of analysis will be censored at the time of the latest date of assessment from their last evaluable efficacy assessment. However, if the patient progresses or dies after two or more missed visits, the patient will be censored at the time of the latest evaluable assessment. Given the scheduled visit assessment scheme, two missing visits will equate to more than 26 weeks since the previous RECIST assessment, allowing for early and late visits. If the patient has no evaluable visits or does not have a baseline assessment they will be censored at day 1 unless they die within two visits of baseline (25 weeks allowing for visit window).

The PFS time will always be derived based on scan/assessment dates not visit dates. Assessments/scans contributing towards a particular visit may be performed on different dates. The following rules will be applied:

Date of progression will be determined based on the earliest of the assessment/scan dates of the component that triggered the progression.

When censoring a patient for PFS the patient will be censored at the latest of the assessment/scan dates contributing to a particular overall visit assessment.

Overall visit assessments will be determined for each assessment (scheduled or unscheduled) and will contribute to the derivation of PFS.

Disease progression is defined as at least a 20% increase in the sum of the diameters of the target lesions (compared to previous minimum sum) and an absolute increase of > 5 mm, or an overall non-target lesion assessment of progression or a new lesion.

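### The PFS censoring rule equates two missed visits with 26 weeks, which fits only 12-weekly scans; once the last scan is at week 60 or later, one missed scan can discard a valid event and lift the tail of the curve

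*Protocol*

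**What the plan says.** Protocol section 8.4.2 (Primary endpoint) gives the rule first in words: "if the patient progresses or dies after two or more missed visits, the patient will be censored" at the latest evaluable assessment. It then converts the words into one figure, by reference to the assessment scheme: "two missing visits will equate to more than 26 weeks since the previous RECIST assessment, allowing for early and late visits". A separate figure of 25 weeks applies to deaths in patients with no evaluable visit or no baseline assessment.

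The scan schedule is stated in several places:

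- Section 5.1.1: "every 12 weeks (±1week) for the first 72 weeks and then every 24 weeks (± 1 week) thereafter".
- Section 5.1.2: "every 12 weeks after enrolment, up to 72 weeks, then every 24 weeks until objective disease progression".
- Table 2, note f: "up to 72 weeks, then every 24 weeks relative to date of enrolment".
- Table 3, note a: "every 12 weeks (±1 week), up to 72 weeks, then every 24 weeks (±1 week) relative to date of enrolment".
- Section 1.5, with the same wording in the synopsis: "at baseline and every 12 weeks relative to date of enrolment, until objective radiological disease progression as determined by the investigator". No change at week 72 is mentioned.

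Section 8.5.1 asks for PFS rates at 6, 12 and 24 months and for updated PFS at the final analysis. PFS in the BRCAm population is a secondary objective.

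**The concern.** One fixed number of weeks cannot represent two missed scans when the interval between scans doubles part-way through follow-up. In the 24-weekly phase, more than 26 weeks without a scan means one missed scan, not two. The words and the number in the same paragraph then classify the same patient differently, and two programmers could derive different data for the primary endpoint.

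The error has a direction, even if scans are missed purely at random, because the rule acts only on patients who have an event. A patient who misses the week-96 scan and is clear at week 120 stays in the risk set throughout. A patient with the same missed scan who has progressed at week 120 is censored back at week 72. Removing the second and keeping the first raises the late part of the Kaplan-Meier curve. In a single-arm trial that curve is the efficacy result.

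**Working it through.** **Inputs.** Scan interval 12 weeks to week 72, then 24 weeks, window ±1 week (5.1.1). Assumed median PFS 8.4 months overall and 19.1 months in BRCAm (8.2). Enrolment Q2 to Q4 2018 and PFS analysis Q2 2020 (synopsis). Study end by Q2 2024 (9.3).

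**The protocol's own figures.** Gap for two missed scans = the two scheduled intervals + 1 week early + 1 week late.
- 12-weekly phase: 2 × 12 + 2 = 26 weeks, as stated.
- From baseline, with one window only: 2 × 12 + 1 = 25 weeks, as stated.

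**The same formula over the whole schedule.**
- Last scan at week 48 or earlier: 26 weeks.
- Last scan at week 60 (weeks 72 and 96 missed): 12 + 24 + 2 = 38 weeks.
- Last scan at week 72 or later: 2 × 24 + 2 = 50 weeks.

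**What one missed scan does under the 26-week figure.**
- Last scan week 72, week 96 missed, progression at week 120: gap 48 ± 2 = 46–50 weeks, always above 26. The event is dropped.
- Last scan week 60, week 72 missed, progression at week 96: gap 36 ± 2 = 34–38 weeks. The event is dropped.
- Last scan week 72, week 96 missed, then death: dropped only if the death is after week 98 (72 + 26).
- No scan missed: the largest in-window gap is 24 + 2 = 26 weeks, which is not more than 26. Nothing is dropped.

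**Who is exposed.** Week 72 is 16.6 months. With exponential PFS, the proportion event-free then is 2^(−16.56/8.4) = 0.255 overall and 2^(−16.56/19.1) = 0.548 in BRCAm. The assumed medians fall at weeks 36.5 and 83, and 24 months is week 104.

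**Size.** A simulation compared the fixed 26-week rule with the 26/38/50-week rule. Assumptions: exponential PFS, 5% of events are deaths, and scans missed independently at 5, 10 or 20%; the protocol gives no rate. Final follow-up is 66–72 months. Each PFS cell reads fixed versus schedule-dependent.

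| Scans missed | Patients of 220 losing a valid event (median 8.4 m) | 36-month PFS, median 8.4 m | 24-month PFS, median 19.1 m | 36-month PFS, median 19.1 m |
|---|---|---|---|---|
| 5% | 5.5 | 6.8 v 6.6% | 45.4 v 45.1% | 31.4 v 30.4% |
| 10% | 9.8 | 7.4 v 6.8% | 46.5 v 46.0% | 33.0 v 31.1% |
| 20% | 15.5 | 9.0 v 7.7% | 49.2 v 48.2% | 36.9 v 33.2% |

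At the 19.1-month median the excess is 0.3, 0.5 and 1.0 points at 24 months, and 1.0, 1.9 and 3.7 points at 36 months. At the 8.4-month median the 24-month rate does not rise (16.3 v 16.4%, 16.9 v 17.0%, 18.5 v 18.5%).

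**Medians at final follow-up.** Overall: the same under both rules (10.83, 10.87 and 10.94 months). At the 19.1-month assumption: 22.08 v 22.08, 22.13 v 22.11 and 22.27 v 22.23 months. These exceed the assumed medians because progression is dated at the scan that finds it.

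**At the planned Q2 2020 cut (18–24 months of follow-up).** 0.5, 0.9 and 1.4 of 220 patients lose an event, and the overall median is identical.

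**The case against.** - **Effect on the main results.** The primary result is a descriptive median, planned for 132 events, with no hypothesis test. Almost nobody is affected at that point and the median does not move. This stands, and it limits the severity.
- **BRCAm median.** Because 19.1 months is week 83, a reader might infer that the BRCAm median is inflated. The calculations do not support that. At final follow-up the two rules differ by at most 0.04 months. At the early cut the fixed rule gives the same or a lower value (21.59 v 21.85 months with 5% missed), against a planned confidence interval of 13.1 to 27.9 months.
- **Deteriorating patients.** A reader might also infer that sicker patients miss more scans, so the bias is larger than shown. That is possible, but the protocol has no data on it and the simulation did not assume it.
- **Unscheduled scans.** Sections 8.4.2 and 8.5.1 use every scan, scheduled or not. Patients on treatment are seen every 4 weeks to week 120, and suspected new sites are to be imaged. Any such scan resets the gap, so the simulated losses may be too high. This lowers the frequency of the problem but leaves the rule wrong.
- **The 12-weekly description.** If scans were 12-weekly throughout, as the synopsis and section 1.5 read, 26 weeks would be correct. Four other places say otherwise, so this is a second inconsistency and not a defence.
- **The SAP.** It may define the window differently. It would then contradict the protocol, which has already fixed a number.

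**Conclusion.** The worded rule is sound; its conversion to 26 weeks is wrong for any patient whose last evaluable scan is at week 60 or later. The fault therefore starts one scan before the change at week 72. A progression found after a single missed scan is then always discarded. A death is discarded only if it falls more than 26 weeks after the last scan.

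The protocol's own definition of premature censoring in section 8.5.1 supports this reading. It uses one scheduled interval plus 2 weeks, which is 24 + 2 = 26 weeks in the later phase. The same gap thus counts as one interval there and as two missed visits in 8.4.2.

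The upward bias is confined to the tail, the updated PFS at the final analysis and, slightly, the 24-month rate at the longer BRCAm median. The direction follows from the rule. The size rests on the assumed 5–20% of scans missed at random, exponential PFS and 5.5–6 years of follow-up. The documents do not support a claim that either median or the 132-event analysis is materially biased. This should be fixed, but it does not threaten the primary result.

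**What to change.** In section 8.4.2, replace the 26-week sentence in one of two ways:

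- count missed scheduled RECIST assessments directly, which stays correct whichever scan schedule is confirmed; or
- state a schedule-dependent window: more than 26 weeks since the last evaluable scan if that scan is the week-48 visit or earlier, more than 38 weeks if it is the week-60 visit, and more than 50 weeks if it is the week-72 visit or later.

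The 38- and 50-week figures assume the schedule in section 5.1.1. Keep the 25-week baseline rule, which is consistent with the first two visits. Reconcile the synopsis and section 1.5 with section 5.1.1 so that a single scan schedule is stated.

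This protocol version is dated January 2023 and the PFS analysis was planned for Q2 2020. Section 8.1 wanted SAP amendments completed before the primary data cut. If the primary analysis has been done, leave it as reported, apply the corrected rule to the updated PFS at the final analysis, and give the 26-week version as a sensitivity analysis.

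The cost is a small protocol and SAP amendment, with the approvals that section 10.5 requires, and one change in the PFS derivation.

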### Secondary endpoints

**Overall Survival**

Overall survival is defined as the time from the date of first dose of olaparib until the date of death due to any cause. Any patient not known to have died at the time of analysis will be censored based on the last recorded date on which the patient was known to be alive.

**Time from first dose to second progression (PFS2)**

Time to second progression is defined as the time from the date of first dose of olaparib to the date of the earliest progression event subsequent to that used for the primary variable PFS or death from any cause. The date of second progression will be recorded by the investigator and defined according to local standard clinical practice and may involve any of objective radiological, symptomatic, CA-125 progression or death. Second progression status will be reviewed every 12 weeks following the progression event used for the primary variable PFS (the first progression) and status recorded. Patients alive and for whom a second disease progression has not been observed should be censored at the last time known to be alive and without a second disease progression, i.e. censored at the last assessment for progression date if the patient has not had a second progression or death.

**Time to first subsequent treatment or death (TFST)**

As a supportive summary to PFS, time to start of first subsequent treatment or death will be assessed. Time to first subsequent treatment or death is defined as the time from the date of first dose of olaparib to the first subsequent treatment start date, or death date. Any patient not known to have had a further subsequent therapy or death will be censored at the last known time to have not received subsequent treatment.

**Time to study treatment discontinuation or death (TDT)**

Time to study treatment discontinuation or death (TDT) will be assessed. TDT is defined as the time from the date of first dose of olaparib to the date of study treatment discontinuation or death from any cause. Any patient not known to have died at the time of analysis and not known to have discontinued study treatment will be censored based on the last recorded date on which the patient was known to be alive.

**Time to second subsequent treatment or death (TSST)**

As a supportive summary to PFS2, time to start of second subsequent treatment or death will be assessed. Time to second subsequent treatment or death is defined as the time from the date of first dose of olaparib to the earlier of the date of second subsequent treatment start date, or death date. Any patient not known to have had a further second subsequent therapy or death will be censored at the last known time to have not received second subsequent treatment.

### Calculation or derivation of safety variable(s)

Safety and tolerability will be assessed in terms of AEs, deaths, laboratory data, and vital signs. These will be collected for all patients. The number of patients experiencing each AE (based on MedDRA preferred term) will be summarized by CTCAE grade.

### Other significant adverse events (OAE)

During the evaluation of the AE data, an AstraZeneca medically qualified expert will review the list of AEs that were not reported as SAEs and discontinuation of investigational product due to adverse events (DAEs). Based on the expert’s judgement, significant adverse events of particular clinical importance may, after consultation with the Global Patient Safety Physician, be considered OAEs and reported as such in the Clinical Study Report. A similar review of laboratory/vital signs will be performed for identification of OAEs. Examples of these are marked haematological and other laboratory abnormalities, and certain events that lead to intervention (other than those already classified as serious), dose reduction or significant additional treatment.

